#### Adverse events

Adverse events in the vitamin A and placebo groups will be tabulated [29]. The denominator will be all enrolled infants. The absolute risk of an adverse event per arm and per adverse event type will be presented.

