### Overview of Study Design

The studies are individually randomized, double-masked, placebo controlled trials. The study participants are neonates who are likely to stay in the study areas until at least 6 months of age, who are able to feed orally at the time of enrolment and whose parents provide written informed consent for study participation. Neonates randomized to the intervention group receive 50,000 IU vitamin A on the day of birth or in the next two days, and those randomized to the control group receive placebo. Potential adverse events are determined during visits by a study worker one day and three days after supplementation. A potential adverse event is defined as any harmful and/or undesired effect as reported by the family which may have resulted from the use of the vitamin A supplement. These include presence of bulging fontanelle, vomiting, fever, diarrhoea, inability to suck or feed, and convulsions. Mortality and morbidity information are collected through periodic home visits by a study worker during infancy (Figure 1).

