##### Monitoring of potential adverse events

After enrolment, each infant is visited by the enrolment team at hospital or home 1 day and 3 days after supplementation to ascertain adverse events. Newborns with adverse events are referred/escorted to the nearest health facility for management.

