### Analysis plan for the three studies

#### Definitions

The primary outcome of the study is defined as a death between supplementation and 180 days of life (6 months). Secondary mortality outcomes are defined as a death between supplementation and 28 days of life, and a death between supplementation and 365 days of life. Severe morbidity is defined as one or more hospitalizations due to any illness between supplementation and day 180 of life. A hospitalization is defined as an admission to hospital as an inpatient, as reported by the mother. Infants will only contribute one hospitalization episode to the analysis, regardless of how many times they were hospitalized in the first six months of life.

Potential adverse events are defined as specific events occurring within 3 days of supplementation. These events include all deaths within 3 days of supplementation; bulging fontanelle confirmed by the research team through a physical examination of the infant; or primary caregiver reports of fever, vomiting, diarrhoea, inability to suck or feed, or convulsions in the first 3 days post supplementation.

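### All enrolled infants are the denominator for every adverse event, although the non-fatal events can be recorded only through a contact; any infant never contacted lowers the stated absolute risk

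*Protocol article*

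**What the plan says.** The Adverse events section of the analysis plan in the Protocol article is short. "Adverse events in the vitamin A and placebo groups will be tabulated", then "The denominator will be all enrolled infants", and "The absolute risk of an adverse event per arm and per adverse event type will be presented". The denominator rule covers all event types alike.

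Other sections say how the events come to be known:

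- **Overview of Study Design:** "Potential adverse events are determined during visits by a study worker one day and three days after supplementation".
- **Definitions:** there are three kinds of event. Deaths: "These events include all deaths within 3 days of supplementation". One sign that needs an examination: "bulging fontanelle confirmed by the research team through a physical examination of the infant". The rest rest on "primary caregiver reports of fever, vomiting, diarrhoea, inability to suck or feed, or convulsions in the first 3 days post supplementation".
- **Monitoring of potential adverse events:** all three sites use the same two visits. For India the text is "each infant is visited by the enrolment team at hospital or home 1 day and 3 days after supplementation". Ghana also asks caregivers to tell the team of unexpected signs within the three days. In Tanzania the question about unexpected signs is part of the visit.
- **Ethical issues:** any death within 72 hours of dosing has its own reporting route to WHO.

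The article gives no expected share of infants with neither visit, and does not say how they are handled.

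**The concern.** The denominator and the numerator do not cover the same infants. The denominator is everyone enrolled. For the six non-fatal event types, the numerator can come only from infants whom a worker saw or whose caregiver reported something. An infant with no contact was not observed, but enters the fraction exactly as an observed infant without symptoms does.

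The quantity is to be presented as an absolute risk of harm from a single dose, in trials meant to inform global policy (Goal of the Ongoing Trials). If some infants are never contacted, each arm's risk is too low and the difference between the arms shrinks by the same fraction. For a safety outcome that is the unwelcome direction.

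The mortality analysis does not share the problem to the same degree. Its primary denominator is person-time (General principles for analysis; Main effects), which allows for incomplete observation. Adverse events have no counterpart to this.

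**Working it through.** The article states no adverse event risk, missed-visit share or safety precision target, so there is no figure of its own to reproduce. The check concerns how the stated rule behaves.

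**Inputs**

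- Denominator: all enrolled infants (Adverse events).
- Ascertainment by visit, report or examination (Overview of Study Design; Definitions; the three site sections on monitoring).
- 32,000 infants in Ghana and in Tanzania (Sample size), taken as 16,000 per arm; equal allocation is my assumption.
- *m*, the share with no adverse event contact at all: assumed 0% to 10%. The 10% loss to follow-up in the Sample size section belongs to the 6-month outcome and does not measure *m*.
- Event risks: assumed, for illustration only.

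**Step 1: one arm.** If infants not contacted have the same risk as the others,

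shown risk = true risk × (1 − *m*).

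For a true risk of 1.0%: *m* = 2% gives 1.0 × 0.98 = 0.98%; *m* = 5% gives 0.95%; *m* = 10% gives 0.90%; *m* = 0 gives 1.0%.

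**Step 2: two arms, equal *m*.** Assumed true risks are 2% on placebo and 3% on vitamin A.

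| *m* | Placebo shown | Vitamin A shown | Difference (points) | Ratio |
|---|---|---|---|---|
| 0% | 2.00% | 3.00% | 1.00 | 1.50 |
| 2% | 1.96% | 2.94% | 0.98 | 1.50 |
| 5% | 1.90% | 2.85% | 0.95 | 1.50 |
| 10% | 1.80% | 2.70% | 0.90 | 1.50 |

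The difference falls by the factor (1 − *m*). In the ratio that factor cancels.

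**Step 3: two arms, unequal *m*.** With 5% not contacted on placebo and 10% on vitamin A, the shown risks are 2% × 0.95 = 1.90% and 3% × 0.90 = 2.70%. The ratio is 2.70/1.90 = 1.42 and the difference 0.80 points. A true ratio of 1.00 is shown as 0.90/0.95 = 0.95. Masking makes a gap of this kind unlikely.

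**Step 4: the assessed denominator.** At *m* = 10% in both arms, 16,000 × 0.90 = 14,400 infants per arm are assessed. The recorded events are 16,000 × 2% × 0.90 = 288 and 16,000 × 3% × 0.90 = 432. Then 288/14,400 = 2.00% and 432/14,400 = 3.00%, the assumed true risks.

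**Step 5: if infants not contacted differ.** Let the risk be *r*c in those contacted and *r*u in those not. The true risk is (1 − *m*)*r*c + *m* *r*u.

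- All-enrolled version: (1 − *m*)*r*c. Its error is −*m* *r*u, so it is low whenever *r*u exceeds zero.
- Assessed version: *r*c. Its error is *m*(*r*c − *r*u).

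The assessed version has the smaller error whenever *r*u is more than half of *r*c. The all-enrolled version is closer only if uncontacted infants have less than half the risk of the others.

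**The case against.** The case for leaving the rule alone has several parts.

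- **Nothing in the text scores unvisited infants as event-free.** A reader might infer such a rule, but the article does not state one; it is a consequence of the denominator. It touches only infants missed at both visits and not otherwise reported. A completed second visit can recover what a missed first visit did not see, since in Tanzania caregivers are asked about the whole time since dosing. Ghana has caregiver reports as well. This stands and limits the point.
- **The size is unknown and may be nil.** This also stands. The India text describes every infant as visited, and at 2% to 5% missed the effect is small.
- **The denominator follows intention to treat.** This stands in part. The General principles section explains that principle as analysis regardless of whether a full dose was received. It does not address outcomes nobody observed. Keeping everyone enrolled does preserve the randomised comparison, a good reason to keep that version alongside.
- **The assessed set has its own weakness.** It conditions on contact after randomisation and would drop infants who die before any visit. This stands, so it should not replace the all-enrolled version outright and should not be used for deaths.

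A reader might also infer that safety will get no comparison between arms and no interval, so that an excess could not be told from chance. The documents do not support that. A condensed article may leave such detail to the full plan, the stated objective is to document adverse effects, and nothing rules a comparison out. The per-arm counts are enough to compute one: 2% against 3% in 16,000 per arm, with none missed, gives a difference of 1.00 point (half-width 0.34) and a ratio of 1.50 (95% interval 1.30 to 1.72).

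**Conclusion.** The point holds as a minor one about the denominator. For the six non-fatal event types, the stated rule makes the absolute risk and the risk difference low by the share of infants with no adverse event contact: 2% to 10% of their value at an assumed share of 2% to 10%. It leaves the ratio unchanged when that share is equal in the arms. This rests on infants without contact having about the same risk as the others. If their risk is different but above zero, the all-enrolled figure is still low, by a different amount.

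The documents do not show that the risks will be understated. That would need some infants with no contact, and the article gives no such figure. Deaths within 3 days have a separate reporting route and are largely outside the point.

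**What to change.** In the Adverse events section, separate the two kinds of event.

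1. **Deaths within 3 days:** keep all enrolled infants as the denominator.
2. **Fever, vomiting, diarrhoea, inability to feed, convulsions and bulging fontanelle:** report the number assessed per arm. Give the risk among infants with at least one adverse event contact (a completed day 1 or day 3 visit, or a caregiver report), with the all-enrolled risk beside it.

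It would help to show how many infants count as assessed only through a spontaneous caregiver report, because they enter the set on account of an event and push the risk slightly upward.

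The cost is a change of analysis wording and some extra tabulation, with no change to trial conduct. It assumes that completion of each visit is recorded. The article describes a standard form for Tanzania but does not say so for every site. The stated risks become slightly higher wherever contacts were missed. The assessed set is conditional on contact after randomisation, and an infant seen only on day 1 is still only partly observed. Showing both versions, with the number assessed, lets the reader judge how much this matters.

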#### Sub-group analyses

The sub-group analyses listed below were specified *a priori *in the trial protocol.

The effect of vitamin A supplementation on all-cause infant mortality from 6 to 12 months by:

- Birth weight (< 1.5 kg, 1.5-1.9 kg, 2.0-2.4 kg, ≥ 2.5 kg, and as a continuous variable)

- Sex (male or female)

- Risk of death before and after receipt of first dose of DTP vaccine. For this analysis, person-time for each infant will be divided into before and after receiving DTP vaccine.

- Economic group (richest to poorest wealth quintiles, using principal components analysis)

- Maternal large-dose vitamin A supplementation (received or not received)

Site-specific results will be presented for all subgroups. Statistical interactions will be assessed using likelihood ratios tests for unadjusted hazard ratios or Wald tests for adjusted hazard ratios. If significance tests yield a p value < 0.01 then site specific mortality rates and hazard ratios comparing mortality in the vitamin A supplementation and placebo group in each sub-group will also be reported.

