### Sample size

The infant mortality rate was estimated to be about 50 per 1000 live births in India and about 60 per 1000 in Ghana and Tanzania. Assuming a 10% loss to follow up, sample sizes at each site were calculated to detect a 15% reduction in mortality from enrolment to 6 months of age, which is the primary outcome, with 85% power and a 5% significance level. The required sample size was 40,200 in India and 32,000 each in Ghana and Tanzania.

This sample size would also be enough to detect a difference of 15% in post-enrolment infant mortality and 20% in post-enrolment neonatal mortality (secondary outcomes).

Blood samples are requested from 720 randomly selected infants at 2 weeks of age and another 720 randomly selected infants and their mothers at 3 months of age at each site. This sample size is sufficient to detect an increase of 0.25 standard deviation (SD) in mean serum retinol in the intervention group after supplementation, with 80% power in each site, and assuming that about 30% families will refuse to allow collection of blood samples.

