#### India

##### Study setting

The study is being conducted in rural sites of Faridabad and Palwal districts, in the state of Haryana, India. The population of the two districts is ~2.1 million. Based on data obtained from a previous trial in the area, the birth rate in this population is 25 per thousand, the infant mortality 60 per thousand live-births per year and the less than six month mortality rate is 50 per thousand live-births per year.

The HIV prevalence among women attending antenatal care in Haryana in the year 2006 was estimated to be 0.13% [22]. Vitamin A deficiency is likely to be a problem in mothers and young children. The prevalence of subclinical vitamin A deficiency based on serum retinol < 20 μg/dl in children aged 3 to 6 years was recently reported as 14.2% [23]. Prevalence of signs and symptoms of vitamin A deficiency among children 5 to 9 years and 10 to 14 years in Haryana was reported to be 15 and 25 per thousand respectively [24]. During the study implementation period there are no programs or research on micronutrients or maternal vitamin A supplementation ongoing in the area. The national program recommends 6 monthly doses of vitamin A (100,000 IU) starting at 9 months of age; the percentage of children 12-35 months of age given vitamin A in the last 6 months in Haryana was 15.9% [25]. In the study areas, around half the families are nuclear; the median number of family members is 6 (5, 8). Around half (52%) of mothers of young children have never been to school; 95% of women do not work outside home. The median (range) family income per year in Year 2010 was Indian Rupees 36,000 (600 to 4600000). The most common sources for seeking care for ill children are private practitioners within and outside of the villages (~ 60%). Over half the deliveries are conducted at home by traditional birth attendants and over 35% of infants are born low birth weight (< 2500 g). Around 40% of under twos have < -2 HAZ and 17% have WHZ score < -2 [26].

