### Timelines

Enrolment of participants started between June and August 2010 in the three studies and is likely to be completed by September 2012. After enrolment is completed, follow up visits will continue to be conducted for a period of 6 months. This will ensure that all enrolled infants have a chance to complete their 6 month follow up. A proportion of enrolled infants will therefore have less than 12 months follow up.

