## Discussion

The three ongoing studies described in this paper are the largest studies evaluating neonatal vitamin A and are expected to provide definitive information to help in formulating policy in favour of or against this intervention. All studies are individually randomized, double blind placebo controlled trials. Each is individually powered to detect a moderate but important effect on mortality in enrolled infants.

The studies are being conducted in Ghana, Tanzania and India and combined with previous studies (conducted in Indonesia, Bangladesh, Nepal, India, Guinea-Bissau and Zimbabwe), will provide information generalizable to Africa and South Asia. There are very few exclusion criteria because the studies are expected to answer a pragmatic question about the effect of routine use of neonatal vitamin A.

The intervention is a single dose of 50,000 international units within the first three days of life, consistent with the previous studies that have tested this intervention. The comparison is placebo with blinding achieved through numbered supplements. This is the most robust design available to ascertain efficacy of an intervention.

The primary outcome for this study was chosen to be mortality in the period from supplementation to 6 months of age. This was done because there is a policy on vitamin A supplementation in the second half of infancy in many developing countries, and the effects of the intervention (neonatal vitamin A supplementation) will be changed by this large supplement provided in the second half of infancy. However, two previous studies from Guinea-Bissau have suggested that the intervention may have a negative effect in the second half of infancy. Therefore, we have added mortality from supplementation until 12 months of age as a secondary outcome in consultation with the DSMB of the study.

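### All five pre-specified subgroup analyses are stated for deaths from 6 to 12 months, a window that is not a defined outcome and leaves out most deaths

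*Protocol article*

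**What the plan says.** All references are to the protocol article.

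- **Sub-group analyses.** One line governs all five subgroups: "The effect of vitamin A supplementation on all-cause infant mortality from 6 to 12 months by". The section describes them as fixed in advance in the trial protocol. For DTP it adds that "person-time for each infant will be divided into before and after receiving DTP vaccine".
- **Definitions.** The main endpoint is set here: "The primary outcome of the study is defined as a death between supplementation and 180 days of life (6 months". Two further mortality endpoints also start at supplementation; one closes at day 28 and the other at day 365. The Objectives and Main effects sections use the same three windows.
- **Timelines.** Follow-up ends 6 months after enrolment closes. "A proportion of enrolled infants will therefore have less than 12 months follow up".
- **Discussion.** Two previous studies raised the possibility of harm in the second half of infancy. The response was that "we have added mortality from supplementation until 12 months of age as a secondary outcome in consultation with the DSMB of the study". The Discussion also says that the subgroup analyses are there to test earlier hypotheses on sex, on time before and after first DTP, and on birth weight.
- **India, Study setting.** "the infant mortality 60 per thousand live-births per year and the less than six month mortality rate is 50 per thousand live-births per year".

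**The concern.** The subgroup window begins where the primary outcome ends and matches neither secondary mortality outcome. Followed as written, the plan never asks whether sex, birth weight or any other listed factor modifies the effect on the primary outcome, although those are the contested questions the subgroups are meant to settle. The window also holds only a small part of the deaths and is the period for which follow-up is admittedly incomplete. The DTP item fits it poorly, because a before/after split at first DTP needs person-time from supplementation onward.

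There is a second cost if the phrase is only a misprint. An analyst who sensibly uses supplementation to 180 days would then depart from the published a priori plan on exactly the questions where pre-specification matters most.

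**Working it through.** **1. Compare the windows.** Primary: supplementation to day 180. Secondary mortality: supplementation to day 28 and to day 365. Subgroups: 6 to 12 months. The subgroup window shares no follow-up with the primary outcome and is only the later part of the 365-day outcome.

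**2. Share of deaths left out (India, Study setting).** Infant mortality is 60 per 1000 live births, of which 50 fall before 6 months, so 60 − 50 = 10 fall from 6 to 12 months. On live births, 50/60 = 83% lie outside the window. Some of the 50 occur before enrolment, and the article does not say how many. With e pre-enrolment deaths per 1000, the share left out is (50 − e)/(60 − e):

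| e (assumed) | share left out |
|---|---|
| 0 | 83% |
| 5 | 82% |
| 10 | 80% |
| 25 | 71% |

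**3. Reproduce the stated sample size, to fix the risk to 6 months.** Inputs from Sample size: 15% reduction, 85% power, 5% significance (taken as two-sided), 10% loss, 1:1 allocation assumed. The control risk from enrolment to 6 months is not stated. Using the two-proportion formula, doubled and divided by 0.90:

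- India at 40 per 1000: about 39,490, or 40,230 with continuity correction; stated 40,200.
- Ghana or Tanzania at 50 per 1000: about 31,290, or 31,880 with correction; stated 32,000.
- Using the infant rates in the Sample size section directly (50 and 60 per 1000) gives about 31,290 and 25,820, which does not match.

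So 40 per 1000 for India is an inference, but one that recovers the plan's figure. It corresponds to e = 10 in step 2. (Sample size gives India's infant mortality as 50 per 1000 and Study setting as 60. That is a separate point; the split at 6 months is available only in Study setting.)

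**4. Expected deaths, India.** Followed: 40,200 × 0.90 = 36,180.

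- Supplementation to 6 months, with the 15% effect: (36,180/2) × 0.040 × (1 + 0.85) = 1,339.
- 6 to 12 months, complete follow-up, no effect assumed in that window: 36,180 × 0.96 × 0.010 = 347.
- Allowing for late enrolees: enrolment runs about 26 months, and follow-up stops 6 months after it ends. With uniform enrolment (assumed), infants enrolled in the last 6 months lose on average half of their 6–12 month person-time. Retained: 1 − 0.5 × 6/26 = 0.885. Deaths: 347 × 0.885 = 307.

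**5. Detectable interaction.** For two equal subgroups and 1:1 allocation, the standard error of the log ratio of hazard ratios is √(16/D). The detectable ratio at 80% power and p<0.01 (the section's own threshold) is exp[−(2.576 + 0.842) × SE].

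| Window | D | SE | detectable ratio |
|---|---|---|---|
| Supplementation to 6 months | 1,339 | 0.109 | 0.69 |
| 6–12 months, complete | 347 | 0.215 | 0.48 |
| 6–12 months, late enrolees partly followed | 307 | 0.228 | 0.46 |

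**6. The before-DTP stratum.** Starting at 6 months removes all earlier person-time, so only infants still without DTP at 6 months contribute. The article gives no schedule or coverage. If 2–20% were unvaccinated then (assumption), at most about 7–69 of the 347 deaths fall in this stratum (0.02 × 347 and 0.20 × 347), fewer once some of these infants are vaccinated later.

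**The case against.** **It is probably a drafting slip.** The Abstract lists the same subgroups straight after the outcomes with no such window, and the DTP split makes sense only from supplementation. The article also points to a full protocol that is not shown and may be right. This stands as an explanation: a reader might infer that the investigators deliberately chose 6–12 months, and the document does not support that. It does not remove the defect, because the printed line is explicit and contradicts the article's own definitions.

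**The second half of infancy is of real interest.** The Discussion gives a reason to look there. But it answers that concern by adding supplementation to 12 months, and it explains the 6-month primary endpoint by noting that later routine supplementation would alter the effect. That supports an extra analysis, not the only subgroup window.

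**The consequences can be overstated.** A reader might infer that the DTP comparison is emptied and unanswerable. Without a schedule or coverage, severe depletion is all that can be said. A reader might apply the four-fifths share to all three trials, but only India gives a split at 6 months. A reader might count only infants with complete 12-month follow-up, which makes the loss of power look worse. The planned analyses use person-time, so partly followed infants still contribute.

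**These are subgroup analyses.** The main analyses are untouched. The three trials' data, with earlier studies if possible, are to be pooled for subgroup effects, and the p<0.01 threshold only triggers further reporting. All true, and it limits the damage. The single-trial plan still names the wrong window for every subgroup.

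**Conclusion.** The point holds as an internal contradiction that should be corrected before unblinding, whether or not it began as a misprint. As written, no subgroup analysis addresses the primary outcome. In India the window omits about 80% of post-enrolment infant deaths, with a range of 71–83% for 25 down to 0 pre-enrolment deaths per 1000. Expected deaths drop from about 1,340 to about 305–350, and the detectable ratio of hazard ratios worsens from about 0.69 to about 0.46–0.48.

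These figures rest on an inferred 40 per 1000 from enrolment to 6 months, 10 per 1000 from 6 to 12 months, 1:1 allocation, uniform enrolment and two equal subgroups, so they describe sex better than the smaller birth-weight strata. For Ghana and Tanzania the direction is likely to be the same, but the documents give no size.

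**What to change.** Before the code is released, check the line against the full trial protocol and reconcile it with Definitions and Main effects. The corrected stem would read: *the effect of vitamin A supplementation on all-cause mortality from supplementation to 180 days (primary) and from supplementation to 365 days (secondary), by:*. State that DTP person-time is split from supplementation onward. Calling the 180-day version primary keeps the two windows from counting as equal sets of tests.

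If the concern about the second half of infancy calls for a 6–12 month analysis, list it separately as additional, and note that it is conditional on survival to 6 months and has incomplete follow-up. Record the date and reason for the correction.

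The cost is one sentence and a dated note. No new data, visits or participants are needed.

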#### Main effects

For the primary outcome, all-cause mortality between supplementation and 180 days of age, data will first be analysed using person time, i.e. infant years of follow up, as the denominator. Hazard ratios and 95% confidence intervals comparing the effect of vitamin A on deaths in the first half of infancy between vitamin A and placebo groups will be calculated using Cox regression. In the unlikely event that there is imbalance between the treatment and control groups, the final statistical models will include adjustment for all imbalanced variables. The effect of vitamin A supplementation on all-cause mortality between supplementation and 180 days of age will also be assessed using enrolled infants as the denominator. The principles outlined above will be followed, and logistic regression will be used to compare mortality in the vitamin A and placebo arms.

The effect of vitamin A supplementation on secondary outcomes (all-cause mortality from supplementation to 12 months, all-cause mortality from supplementation to end of the neonatal period, hospitalizations) will be assessed using similar methods to the primary analysis; both person time and enrolled infants will be used as denominators for all analyses.

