We have several subgroup analysis decided *a priori*. These subgroup analyses are planned to confirm or refute hypotheses raised by previous studies and systematic reviews. A pooled analysis of two studies from Guinea-Bissau raised the hypothesis that the intervention may have a negative effect in girls, but a meta-analysis of all available trials did not find this interaction. The studies from Guinea-Bissau have also raised the hypothesis that effects may be different before or after the first dose of DTP immunization. A meta-analysis hypothesized that the effects may be different in low or normal birth weight infants and by the level of vitamin A deficiency in populations.

The biological rationale for the potential effect of neonatal vitamin A is not known. It has been hypothesized that the intervention could work through positively affecting the immune system or by promoting the maturation and integrity of the epithelium. A set of parallel animal and human studies is being conducted to understand the transport and metabolism of the neonatal vitamin A dose and its effects on the innate and adaptive immune system. These studies will shed more light on the potential biological mechanisms through which this intervention may work.

However, policy formulation will largely be based on the results of efficacy of the intervention from the ongoing randomized controlled trials. These results will be combined with results of previous studies in a new meta-analysis for an overall effect. The data from the three new studies, as well as previous studies if possible, will be pooled to carefully examine subgroup effects.

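### The before/after-DTP split does not separate DTP from age, so a vitamin A effect that only changes with age can be reported as a DTP interaction; the printed 6–12 month window must be reconciled first

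*Protocol article*

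**What the plan says.** Protocol article, Sub-group analyses. The list opens with one window for every subgroup: "The effect of vitamin A supplementation on all-cause infant mortality from 6 to 12 months by". For DTP, "For this analysis, person-time for each infant will be divided into before and after receiving DTP vaccine". The test is given as "Statistical interactions will be assessed using likelihood ratios tests for unadjusted hazard ratios or Wald tests for adjusted hazard ratios". A reporting rule follows: "If significance tests yield a p value < 0.01 then site specific mortality rates and hazard ratios" by subgroup are also reported.

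Protocol article, Main effects. The only covariate adjustment described depends on imbalance between the arms: "the final statistical models will include adjustment for all imbalanced variables". No term for treatment by age is stated.

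Protocol article, Discussion. The subgroup analyses are meant to confirm or refute earlier hypotheses, and one of these is that "effects may be different before or after the first dose of DTP immunization". The same section cites earlier studies suggesting that "the intervention may have a negative effect in the second half of infancy".

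**The concern.** Every infant starts follow-up before DTP, and vaccinated infants pass to the after-DTP category only at older ages. DTP status is therefore tied to age and to time since the single dose. A Cox model on the age scale lets the baseline hazard vary freely with age, so it absorbs the fall in mortality with age. It does not absorb a change with age in the hazard ratio for vitamin A. Without a term for that change, the treatment-by-DTP term picks it up. The null hypothesis actually tested is then close to an equal vitamin A effect at younger and older ages, which is a different question from whether DTP modifies the effect. Randomisation does not protect against this, because DTP status arises after randomisation.

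At stake is how a significant result is read. A dose that protects early and then fades could pass the P < 0.01 rule and be presented under the DTP heading, with consequences for views on vaccination as well as on supplementation.

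**Working it through.** **1. Reproduce the plan's own figure.** The DTP analysis has no stated size or power; its only figure is P < 0.01. The site sample sizes do indicate the 6-month control risk. The formula is total N = 2 × (1.960 + 1.036)² × [p₁(1−p₁) + p₂(1−p₂)] / (p₁−p₂)² / 0.90, with p₂ = 0.85p₁.
- p₁ = 0.04 gives about 39,500 (plan, India: 40,200).
- p₁ = 0.05 gives about 31,300 (plan, Ghana and Tanzania: 32,000).
- p₁ = 0.06 gives about 25,800, which matches no site.

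So 6-month risks of about 40 and 50 per 1000 are used below. This is an inference, because the Sample size section gives only infant mortality.

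**2. Assumptions not in the document.** Main set: 28,800 infants (32,000 less 10%) at 50 per 1000, or 36,180 (40,200 less 10%) at 40 per 1000; 40–60% of deaths by day 28; first DTP spread over days 42–75 with 95% coverage, or days 42–120 with 90%. A second set used weekly age bands, a median first-DTP age of 6.5–12 weeks and 90% coverage. True DTP modification is zero throughout.

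**3. One case by hand, follow-up from supplementation to 6 months.** Site of 32,000, second set, median first DTP at 8 weeks, hazard ratio (HR) 0.80 before 4 weeks and 1.00 after. Expected deaths are 949 before and 486 after DTP. The stratum HRs are 0.835 and 1.000.
- 0.835 is a mixture: 0.80w + 1.00(1−w) = 0.835 gives w = 0.825, so about 82% of control deaths before DTP fall in the first 4 weeks.
- Ratio of hazard ratios (after/before) = 1.000/0.835 = 1.20; log = 0.180.
- SE = √(4/949 + 4/486) = 0.112.
- z = 0.180/0.112 = 1.62. Rejection at P < 0.01 = Pr(Z > 2.576 − 1.62) = 0.17.

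Milder trend, 0.80 then 0.90. The before-DTP HR is 0.80 × 0.825 + 0.90 × 0.175 = 0.8175, and the ratio is 0.90/0.8175 = 1.10. Deaths become about 940 and 462, SE = 0.114, z = 0.85, and rejection is 0.04.

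Constant HR 0.85: ratio 1.00, rejection 0.01.

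**4. Ranges over the assumptions.**

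| True age pattern, no DTP effect | Apparent ratio | Rejection at P < 0.01 |
|---|---|---|
| Constant 0.85 | 1.00 | 1% |
| 0.80, then 0.90 after day 28 | 1.07–1.11 | about 3–4% |
| 0.80, then 1.00 after day 28 | 1.14–1.21 | about 9–18% |

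The second set gives 1.17–1.21 and 11–21% for the last row. Steeper patterns, such as 0.80 then 1.20, reach 45–75%, but nothing in the document points to a change that large within six months.

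**5. With treatment-by-age bands added.** The apparent ratio returns to 1.00–1.03 and rejection to about 1%. A single log-age term is not enough: rejection ranges from 1% to 13% over the patterns tried. The SE of the log ratio rises from about 0.11–0.13 to 0.18–0.30.

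**6. The printed 6–12 month window.** With 90–95% coverage and an age trend in the HR from 0.85 to 1.4, the ratio is 1.00 and rejection 1%, because DTP status hardly changes with age in that period. However, only 5–10% of person-time is before DTP, with about 16–32 deaths against 288–304 after. SE = √(4/32 + 4/288) = 0.37 to √(4/16 + 4/304) = 0.51. For 80% power at P < 0.05 the true ratio would have to be about exp(2.80 × 0.37) = 2.8 to exp(2.80 × 0.51) = 4.2.

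**The case against.** The strongest objection is the window. The article prints 6 to 12 months for every subgroup, and there the confounding does not arise. This stands, and it makes the concern conditional. It does not rescue the analysis, because that window leaves almost nothing before DTP to compare.

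Second, this is a condensed article, and the full protocol or analysis plan may contain the missing term. That also stands. The published text nevertheless fixes both the split and the test, and as stated they do not isolate DTP. If the term exists elsewhere, one sentence closes the point.

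Third, the hypothesis is worded only as a difference before and after DTP, which the split does describe, and the article does not say that a difference would be attributed to the vaccine. This is fair: reporting as DTP modification can happen but is not automatic. The analysis is, though, meant to confirm or refute a DTP hypothesis, so the limit on interpretation belongs in the plan.

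Fourth, the separate 28-day, 6-month and 12-month mortality results would show a fading effect to an attentive reader. That helps interpretation but does not correct the interaction test.

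Finally, the remedy loses precision, and vaccinated and not-yet-vaccinated infants of the same age may differ in health and access to care. Both are true, so the added model should stand beside the split and not replace it.

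**Conclusion.** The point holds in conditional form. If the analysis covers time from supplementation, the stated split and test confound DTP status with age and time since dosing. A vitamin A effect that only changes with age can then be reported as a DTP interaction. The false-positive rate at P < 0.01 is about 9–18% if the effect vanishes after day 28, about 3–4% if it weakens from 0.80 to 0.90, and 1% if it is constant. These figures rest on assumed DTP timing, coverage, neonatal share of deaths and age-specific hazard ratios. In the window as printed the error is absent, but the DTP question can hardly be answered.

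Three stronger readings are not supported:
- **That the planned test will produce a DTP finding.** Even when the effect vanishes after day 28, most trials would not cross P < 0.01.
- **That detectable differences of 20% for neonatal and 15% for 6-month mortality show an expected early effect.** They are design sensitivities for outcomes with different numbers of events. The Discussion's possible harm concerns the second half of infancy, so the document raises age variation without giving its size before six months.
- **That an opposite age trend would hide a true DTP effect.** This is possible in principle, but it has not been calculated here.

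**What to change.** 1. Reconcile the window printed above the subgroup list with the DTP question. State for the DTP analysis a period that contains time before and after first DTP, such as supplementation to 6 months.
2. Keep the before/after split, and state that a difference in it will not be attributed to DTP on its own, because DTP status is confounded with age and time since dosing.
3. Beside it, fit a Cox model on the age scale with DTP as a time-varying covariate, a treatment-by-DTP term and treatment-by-age-band terms (for example under 28, 28–59, 60–89, and 90 days and over). Report both results.
4. State that comparing vaccinated with not-yet-vaccinated infants of the same age is non-randomised.

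**Cost.** Wording and one extra model per site. No new data are needed, because age at death is recorded and time of first DTP is already to be tabulated. The price is precision: the SE of the log ratio roughly doubles. For a true change from 0.80 to 1.00 at DTP (log ratio 0.223), SEs of 0.18–0.30 give about 12–24% power at P < 0.05 in one site, and 3–9% at P < 0.01. The question would therefore rest mainly on the pooled subgroup analysis foreseen in the Discussion. Dividing the SE by √3 for three similar sites gives roughly 25–57% at P < 0.05, so a null result there should not be read as refuting the hypothesis.
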